## Abstract

**Introduction::**

Chronic obstructive pulmonary disease (COPD) is an illness characterized by progressive aggravation of airflow limitation, which seriously affects patients’ quality of life, and even life-threatening. The lung function of COPD patients is chronically and progressively deteriorated. Among them, the lung function of early COPD patients deteriorates rapidly, and forced expiratory volume in 1 second (FEV_1_) declines faster than other stages. If diagnosed early and effectively treated in time, it can greatly affect the prognosis. As a traditional exercise regimen, Baduanjin can improve lung function, exercise capacity, and quality of life of COPD patients. However, high-quality evidence-based medical evidence is so far be lacking to confirm the effectiveness of Baduanjin in reducing or preventing mild COPD lung function decline.

**Methods::**

This study is a randomized controlled trial, 192 patients with mild COPD were randomly divided into experimental group and control group. Both of them will receive basic treatment (health education and Tiotropium bromide), the experimental group will receive Baduanjin exercise training, and the control group will be told to maintain the original lifestyle and control the exercise. The Baduanjin exercise will last for 24 weeks and will be followed up for 72 weeks. The primary outcome is the change in lung function, including FEV_1_, FEV_1_/forced vital capacity (FVC), and FEV_1_/predicted. The secondary results included COPD assessment test, 6-minute walk test, St. George Respiratory Questionnaire, and Dyspnea Scale. Safety will also serve as assessing during the test.

**Discussion::**

The results of this trial will provide that traditional Baduanjin exercises can prevent COPD lung function deterioration, and provide a simple, inexpensive, and daily pulmonary rehabilitation measure for the patients with mild COPD.

## Introduction

1

Chronic obstructive pulmonary disease (COPD) is an illness characterized by the progressive aggravation of respiratory symptoms and airflow obstruction. Its morbidity and mortality are one of the highest in the world, causing a huge burden on society and the economy.^[1]^ According to estimates by the World Health Organization (WHO), COPD will rise to the third leading cause of death in the world by 2030^[2]^ if no control measures are applied. The global initiative for chronic obstructive pulmonary disease (GOLD) uses the ratio of forced expiratory volume in 1 second to forced vital capacity (FEV_1_/FVC) <0.70 as the diagnostic criteria for airflow obstruction. On this basis, COPD is divided into 4 phases based on the degree of FEV_1_ decline,^[3]^ the proportion of GOLD I and II stages is much higher than that of III and IV.^[4]^ In a retrospective studies, Tantucci and Modina^[5]^ found that the average decline rate of FEV_1_ in GOLD II and III phases was 47 to 79 mL/yr and 56 to 59 mL/yr, respectively, and in GOLD IV, it was lower than 35 mL/yr; Bhatt et al^[6]^ also found that FEV_1_ of COPD patients with GOLD stage I decline fastest, and then gradually slowed down. With the decline of lung function, COPD patients gradually develop to skeletal muscle dysfunction, which affects the patient's athletic ability, reduces the quality of life, and produce anxiety and depression.^[7,8]^ Studies by Burkes and Drummond^[9]^ and Lee et al^[10]^ have shown that early intervention (knowledge education, drug therapy, exercise therapy, etc) for COPD can effectively delay the disease process, improve the mental state of patients, increase exercise tolerance, and reduce social and economic burdens. Therefore, it is necessary to intervene as early as possible.

Pulmonary rehabilitation is an important tool for non-drug treatment of COPD, including but not limited to sports training and education management.^[11]^ Although numerous studies have confirmed that pulmonary rehabilitation can effectively delay the decline of lung function, improve exercise capacity and quality of life in COPD patients.^[12]^ But it has not been fully used due to limitations of venues, equipment, professionals.^[13,14]^ A systematic analysis also indicated a lack of high-quality evidence for the efficacy of traditional pulmonary rehabilitation in mild COPD.^[15]^ Therefore, a simple, easy, safe, and effective pulmonary rehabilitation method for mild COPD is needed. Baduanjin is a traditional Chinese exercise regimen with moderate activity, which can effectively exercise breathing and muscle strength of the limbs, adjust the mental state, and is easy to learn, not restricted by the venue, is very suitable for COPD patients.^[16]^ Previous clinical studies and system analysis have shown that Baduanjin can improve lung function, exercise endurance, and quality of life in COPD patients,^[17–19]^ but it lacks high-quality clinical evidence-based evidence. Therefore, we hypothesized that Baduanjin can delay the decline of lung function, improve exercise ability and quality of life in patients with mild COPD, and designed this experiment for verification.

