### Design

2.1

This study is a randomized, parallel, and controlled trial designed to evaluate the effectiveness of Baduanjin exercise intervention in improving lung function, exercise capacity, and quality of life in patients with mild COPD. A total of 192 patients will be recruited in Chengdu and randomly assigned to the experimental group or the control group in a 1:1 ratio. Participants in the experimental group will receive a 24-week Baduanjin exercise training intervention at least 5 days a week and 60 minutes a day, while participants in the control group will not be given any specific exercise intervention and will be told to maintain their original lifestyle for 24 weeks. The primary and secondary outcomes will be measured at baseline and at weeks 12, 24, 36, 48, 72, and 96. The participation process of this trial is shown in Fig. 1. This agreement follows the standard agreement item: Intervention Test Recommendation (SPIRIT) guidelines,^[20]^ and meets the SPIRIT list (please see Guidelines Checklist). The study flow chart is presented in Fig. 2.

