### Outcome measures

3.2

Primary outcome: The primary outcome is the change in lung function from baseline to the end of the follow-up period (all time points). Including FEV_1_, FVC, FEV_1_/predicted value.

Secondary outcomes: Including COPD assessment test (CAT), 6 minute walking test (6MWT), dyspnea score (modified British medical research council dyspnea score, mMRC), and St. George Respiratory Questionnaire (SGRQ), Self-rating Depression Scale (SDS), Self-rating Depression Scale (SAS).

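### The hypothesis and expected conclusion concern slower lung-function decline, but the primary outcome is change from baseline and no stated test addresses a rate

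*Protocol article*

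**What the plan says.** The Protocol article states its purpose in three places, and they differ.

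- Introduction (section 1): "we hypothesized that Baduanjin can delay the decline of lung function".
- Design (section 2.1): the trial is "designed to evaluate the effectiveness of Baduanjin exercise intervention in improving lung function, exercise capacity, and quality of life".
- Abstract, Discussion: "The results of this trial will provide that traditional Baduanjin exercises can prevent COPD lung function deterioration".

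On measurement, section 3.2 says "The primary outcome is the change in lung function from baseline to the end of the follow-up period (all time points"), covering FEV1, FVC and FEV1/predicted. Section 2.1 adds: "The primary and secondary outcomes will be measured at baseline and at weeks 12, 24, 36, 48, 72, and 96". Training lasts 24 weeks and is followed by 72 weeks of follow-up.

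Section 3.6 names a group t test or non-parametric test between arms and a paired t test or non-parametric test against baseline, with last observation carried forward. It names no slope, group-by-time term or post-training change. Section 2.4 sizes the trial on FEV1% means of 57.09 and 60.24, which is a difference in level, and attaches no time point to it.

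For background, the Introduction reports that the average yearly FEV1 decline in GOLD II and III "was 47 to 79 mL/yr and 56 to 59 mL/yr, respectively". It says that stage I, the population of this trial, declines fastest, but gives no figure for it.

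**The concern.** Delaying or preventing decline is ordinarily a statement about rate. Change from baseline is a statement about level. If training produces a lasting gain in measured FEV1 and both arms then decline in parallel, the difference in change from baseline is positive although the rate of decline after training is the same in both arms. If training slows decline, the difference is positive too. The tests in section 3.6, applied visit by visit, return the same kind of answer in both cases.

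At stake is the headline claim. The abstract already words the expected result as prevention of deterioration, and a significant primary result as defined would not establish that.

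**Working it through.** **1. The passages side by side.** The Introduction and the abstract's Discussion speak of decline. Section 2.1 (improving), section 2.4 (FEV1% means), section 3.2 (change from baseline) and section 3.6 (group and paired tests) speak of level. No stated outcome or test estimates a rate.

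**2. Two mechanisms with the same week-96 result.** Assume a control decline of 60 mL/yr, which lies inside the cited GOLD II range.

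- Slower decline: the rate is halved throughout, so the difference at week w is 60 × 0.5 × w/52.
- One-off gain: the same final difference is built up linearly to week 24, with equal slopes afterwards.

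| Week | 12 | 24 | 36 | 48 | 72 | 96 |
|---|---|---|---|---|---|---|
| Slower decline (mL) | 6.9 | 13.8 | 20.8 | 27.7 | 41.5 | 55.4 |
| One-off gain (mL) | 27.7 | 55.4 | 55.4 | 55.4 | 55.4 | 55.4 |

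The week-96 change is identical. The week 24–96 slopes differ by 30 mL/yr in the first case and 0 in the second. With 47 or 79 mL/yr in place of 60, the shared week-96 difference is 43.4 or 72.9 mL.

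**3. How the tests behave.** Simulation of the same two mechanisms used 77 per arm and 2,000 runs per setting, with assumed within-patient SD of 80–150 mL and SD of individual slopes of 40–60 mL/yr. Share of runs significant at 5%:

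| Test | One-off gain | Slower decline |
|---|---|---|
| Week-96 change from baseline | 31–72% | 31–73% |
| Week 24–96 slope | about 5% | 25–63% |

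The change test does not discriminate. The slope test does, with limited power.

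**4. Scale against the planning figure.** The plan's difference is 60.24 − 57.09 = 3.15 points of FEV1%. Use the GOLD II rates of 47–79 mL/yr, since there is no stage I figure, and an assumed predicted FEV1 of 2.5–3.5 L. If decline were halted completely, the gain would be:

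- Week 24: 47 × 24/52 = 21.7 mL to 79 × 24/52 = 36.5 mL. As points, 21.7/3500 = 0.6% to 36.5/2500 = 1.5%.
- Week 96: 47 × 96/52 = 86.8 mL to 79 × 96/52 = 145.8 mL. As points, 86.8/3500 = 2.5% to 145.8/2500 = 5.8%.

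The 3.15 points lie above the week-24 range and inside the week-96 range. This is illustration only: the rates are for another stage, and the 3.15 has no stated visit. It is also a weak benchmark, because the inputs in section 2.4 do not give the stated 77 per group. With SD = √((22.53² + 20.15²)/2) = 21.37, n = 2 × (1.960 + 1.282)² × 21.37²/3.15² ≈ 968 per group. That is a separate problem.

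**The case against.** Four arguments count against the point.

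- **The outcome covers all time points, four of them after training ends.** A constant gap from week 24 to 96 would suggest a lasting gain, and a widening gap would suggest continuing slower decline. This stands. A reader might infer that the trial cannot separate the two, but the data could help to do so; what is missing is a summary or test that uses them this way.
- **Section 2.1 states a level aim, which the outcome answers.** This also stands, and it makes the defect an inconsistency between statements of purpose. One can add that a lasting gain delays the moment at which a patient reaches any given FEV1. That reading of *delay* is possible, but it does not carry over to preventing deterioration.
- **An unseen analysis plan may contain a slope model.** It may. The point, however, rests on what the article itself states: a hypothesis, a primary outcome, tests and an expected conclusion that do not match.
- **The abstract's sentence is not a decision rule.** Correct. Nowhere does the protocol say that a week-24 difference will be reported as prevention of decline.

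A reader might also infer that the plan would miss a real late slowing. The document does not support that: later slowing enlarges the week-72 and week-96 changes, which are inside the primary outcome, and in the simulation the week-96 change test detects it at least as often as the slope test.

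**Conclusion.** The concern holds as a mismatch between claim and measure. A significant change from baseline at a single visit does not by itself support delayed or prevented decline, because a one-off gain and slower decline can produce the same difference (55.4 mL at week 96 in the illustration). That equality does not depend on the assumed 60 mL/yr; only its size does. The simulated rejection rates rest on assumed SDs, since the protocol gives no SD of change or of slope.

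Two stronger inferences should not be drawn. One is that a 3.15-point difference at week 24 would have to be mainly a level shift: section 2.4 ties that figure to no visit, and the cited rates are for GOLD II while stage I is said to decline faster. The other is that only the week 24–96 slope could ever count as evidence on decline. Slowing confined to the training period leaves a constant later difference (30 × 24/52 = 13.8 mL in the illustration), which no analysis of these visits can tell from a one-off gain of that size.

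**What to change.** 1. Keep change from baseline in section 3.2 as the level outcome, supporting statements about improvement.
2. Add to sections 3.2 and 3.6 a pre-specified secondary between-arm comparison of FEV1 trajectory, from a repeated-measures model over all visits with a group-by-time effect and separate slopes to week 24 and from week 24 to 96. Fit it to observed values, since carrying forward the last value holds a declining measure flat.
3. Reserve *delay* and *prevent decline* for a result that this analysis supports, and state that slowing confined to training cannot be distinguished from a one-off gain.
4. Align the abstract's Discussion, the Introduction and section 2.1.

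If no rate analysis is added, restate the hypothesis and the expected conclusion as a difference in level.

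No new visits or tests are needed; the cost is protocol wording and some analysis work. The slope contrast is less precise than the level difference and the trial is not sized for it, so a claim about decline becomes harder to reach. Keeping the analysis secondary avoids a second primary question that would need its own multiplicity rule.

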## Methods/design

2

### Design

2.1

This study is a randomized, parallel, and controlled trial designed to evaluate the effectiveness of Baduanjin exercise intervention in improving lung function, exercise capacity, and quality of life in patients with mild COPD. A total of 192 patients will be recruited in Chengdu and randomly assigned to the experimental group or the control group in a 1:1 ratio. Participants in the experimental group will receive a 24-week Baduanjin exercise training intervention at least 5 days a week and 60 minutes a day, while participants in the control group will not be given any specific exercise intervention and will be told to maintain their original lifestyle for 24 weeks. The primary and secondary outcomes will be measured at baseline and at weeks 12, 24, 36, 48, 72, and 96. The participation process of this trial is shown in Fig. 1. This agreement follows the standard agreement item: Intervention Test Recommendation (SPIRIT) guidelines,^[20]^ and meets the SPIRIT list (please see Guidelines Checklist). The study flow chart is presented in Fig. 2.

**Figure 1 F1:**
[figure not shown]
Spirit figure of enrollment, interventions, and assessments. [1] Basic treatment: health education and Tiotropium bromide; [2] lung function test: FEV_1_, FVC, FEV_1_/predicted; [3] Dyspnea score: modified British medical research council dyspnea score; [4] SGRQ score: St. George Respiratory Questionnaire; [5] SDS: Self-rating Depression Scale; [6] SAS: Self-rating Depression Scale.

**Figure 2 F2:**
[figure not shown]
Flowchart of the study design.

### Ethics approval

2.2

The study is in compliance with the Declaration of Helsinki (Edinburgh 2000 versions). The research program has been approved by the Chinese Ethics Review Committee for Registered Clinical Trials (Approval No. ChiECRCT20200189), and the members of the ethics committee tracked the design and implementation of the research. We registered the study in the Chinese Clinical Trial Registry (Registration No. ChiCTR2000035109) in 2020. If there is any amendment to the protocol, approval must be again sought from the Ethics Committee.

### Recruitment

2.3

Participants will be recruited through local advertisements and doctors from the Department of Respiratory Medicine, Affiliated Hospital of Chengdu University of Traditional Chinese Medicine. Before recruiting, participants will be provided with details about the clinical study, including its purpose, grouping methods, the differences between the experimental group and the control group, study schedule, and possible risks and benefits. Recruiters will explain to patients that the basic treatments of the 2 groups are according to the guidelines recommended by the GOLD^[3]^ and the “Guidelines for the Diagnosis and Treatment of Chronic Obstructive Pulmonary Disease (2013 Revised Edition),”^[21]^ and that Baduanjin exercise training is a safe and effective pulmonary rehabilitation measure to ensure that subjects can receive randomization and in strict accordance with the protocol. All patients will be required to sign informed written consent prior to beginning any research procedure.

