### Blinding

2.6

Due to the particularity of sports training, the participants, coaches, and follow-up personnel cannot be blinded, we will blind the result assessors through the following methods to ensure the reliability of the results. The results will be evaluated by a new person not involved in the previous experiment. Participants, sports coaches, and research assistants will be advised not to disclose any information about the assignment before the outcome evaluation begins. Therefore, the outcome evaluator will not know the assignment of the protocol until the end of the study.

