## Discussion

4

COPD is a major public health problem that seriously affects the quality of life of patients, even life-threatening. The sign of COPD progression is decreased lung function, and pulmonary rehabilitation has been proven to be the most effective treatment strategy for improving shortness of breath, health status, and quality of life.^[13]^ However, traditional pulmonary rehabilitation requires a series of professional evaluations to develop a perfect and personalized plan,^[22]^ so the overall effect is not satisfactory, and it is urgent to develop family-based pulmonary rehabilitation methods.^[23]^ Baduanjin is the representative of the traditional Chinese medicine guidance method, covering endurance training, breathing muscle training, stretching training, and psychological adjustment required for pulmonary rehabilitation. The whole set of movements is easy to learn, moderate intensity, and significant efficacy, which applicability and cost are much better than traditional pulmonary rehabilitation. However, previous studies have mostly focused on the efficacy of Baduanjin in the middle and late stages of COPD, and there is no unified understanding of its intervention effect in mild COPD pulmonary function decline. Therefore, this study focuses on the effect of Baduanjin on lung function in the early stage of COPD.

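### Recruiters present Baduanjin to all candidates as safe and effective, although the protocol treats its effect in mild COPD as unproven; this may add avoidable expectation bias to the self-reported secondary outcomes

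*Protocol article*

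**What the plan says.** Section 2.3 (Recruitment) sets out what recruiters tell candidates. Besides explaining that both arms receive guideline-based basic treatment, they are to say that "Baduanjin exercise training is a safe and effective pulmonary rehabilitation measure to ensure that subjects can receive randomization"; the same sentence gives adherence to the protocol as a further aim. Candidates also hear the purpose of the study, its possible risks and benefits, and "the differences between the experimental group and the control group". The section ends: "All patients will be required to sign informed written consent prior to beginning any research procedure".

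Elsewhere the article describes the state of knowledge differently:

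- Section 2.1 (Design) says the trial is "designed to evaluate the effectiveness of Baduanjin exercise intervention in improving lung function, exercise capacity, and quality of life" in patients with mild COPD.
- The Introduction cites earlier studies that report benefit in COPD, "but it lacks high-quality clinical evidence-based evidence". The Abstract makes the same point about lung-function decline in mild COPD specifically.
- The Discussion says earlier work mostly concerned middle and late disease and that "there is no unified understanding of its intervention effect in mild COPD pulmonary function decline". It also describes this trial as, to the authors' knowledge, the first of Baduanjin training in mild COPD.

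On masking, section 2.6 says that "the participants, coaches, and follow-up personnel cannot be blinded", and for the people who measure outcomes, "we will blind the result assessors through the following methods to ensure the reliability of the results". Under section 2.5 the allocation envelope is opened only after consent and baseline assessment.

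**The concern.** Patients are told as fact something close to what the trial is meant to find out. Both arms hear it before randomisation, but its consequences differ once the envelope is opened. One arm receives the exercise that was described as effective; the other is told to keep its usual lifestyle and receives no training (section 3.1.2). Because this divergence starts after baseline, analysing change from baseline does not cancel it.

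The outcomes most open to such a divergence are those on which the patient supplies the answer. Section 3.2 lists six secondary outcomes, five of them questionnaires or self-rated scales. Quality of life and exercise capacity are named trial aims, so a difference on these measures would be read as benefit. Part of it could reflect what patients were led to expect. Some expectation is unavoidable in an unblinded exercise trial, but a part created by the recruitment message can be avoided.

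**Working it through.** The plan states no figure on this point, so the check is mainly textual, followed by an illustration of scale.

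**Step 1. The message against the protocol's own account of the evidence.** Section 2.3 makes an unqualified statement of effectiveness and safety. The Abstract, Introduction and Discussion say the evidence is weak in quality and the effect in mild disease unsettled. Section 2.1 makes effectiveness the research question, and section 3.4 still plans to assess safety. The evidence for benefit that the article cites comes mostly from more advanced disease than the population enrolled here (FEV1 at least 80% of predicted, section 2.8). The message is therefore firmer than the article's own reading of the evidence.

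**Step 2. Which outcomes are exposed.**

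| Outcome (section 3.2) | Who determines the value | Does assessor blinding help? |
|---|---|---|
| CAT, mMRC, SGRQ, SDS, SAS | the unblinded patient's own report | no, not against the patient's expectation |
| 6-minute walk test | measured, but depends on patient effort | partly |
| FEV1, FVC, FEV1/predicted (primary) | spirometry; some effort dependence | largely |

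**Step 3. Illustration of scale.** Inputs from section 2.4: two-sided alpha 0.05; 77 per arm before the dropout allowance and 96 per arm after it. Assumed, because the documents give no value: there is no true effect, and the total arm-dependent shift in self-report is b = 0.1, 0.2 or 0.3 SD. For a two-group comparison of means under the normal approximation:

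- noncentrality = b × √(n/2)
- rejection probability = 1 − Φ(1.96 − noncentrality) + Φ(−1.96 − noncentrality)

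| b (SD, assumed) | n = 77: noncentrality | n = 77: rejection | n = 96: noncentrality | n = 96: rejection |
|---|---|---|---|---|
| 0 | 0 | 5.0% | 0 | 5.0% |
| 0.1 | 0.62 | 9.5% | 0.69 | 10.7% |
| 0.2 | 1.24 | 23.7% | 1.39 | 28.3% |
| 0.3 | 1.86 | 46.1% | 2.08 | 54.7% |

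These are rates for one outcome in one comparison. They show how sensitive the questionnaires are to a modest total shift. They do not measure what the sentence in section 2.3 contributes: b covers all expectation in an unblinded comparison with no training, and the documents give no basis for dividing it.

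**The case against.** The strongest reply has four parts.

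**The sentence is general.** It calls Baduanjin an effective rehabilitation measure and does not claim that it slows decline in mild disease. The Introduction does cite earlier studies showing benefit in COPD. This stands in part: the overlap with the trial question is incomplete. But the listener is a candidate with mild COPD who will naturally apply the statement to himself or herself, and section 2.1 counts exercise capacity and quality of life as part of the question.

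**Candidates are told the purpose, risks and benefits, and the actual recruitment text is not shown.** This also stands in part. A neutral statement may exist in material that was not available, so nothing can be concluded about the consent form. The article nevertheless describes the content of the message and its aim, and that description contains no offsetting statement of uncertainty.

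**Patients cannot be blinded, so expectation bias would exist anyway.** This stands and limits the claim. Neutral wording would not bring the rejection rates back to 5%. It would only take away the avoidable part.

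**Assessors are blinded and the primary outcome is spirometry.** This stands for the primary outcome, which is why the point is confined to the secondary ones. It does not help where the patient provides the score.

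**Conclusion.** The point holds in a limited form. The recruitment message is not neutral and does not fit the protocol's own statement of the evidence. In an unblinded trial it may push the five self-reported secondary outcomes, and possibly the 6-minute walk test, in favour of Baduanjin. The size of that push is unknown. The illustrative range of about 10% to 46% rejection at 77 per arm rests on an assumed total shift of 0.1 to 0.3 SD with no true effect.

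A reader might infer three stronger things that the documents do not support.

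- *That the inflated rejection rates are caused by this sentence.* They describe all expectation together, much of which would remain under neutral wording.
- *That retention will be biased towards Baduanjin.* Disappointed controls might leave, but section 2.9 also withdraws patients whose exercise time is below 80% of that prescribed, and only the Baduanjin arm has an exercise prescription. Under the last-observation-carried-forward rule in section 3.6, a control who leaves early while FEV1 is falling contributes an earlier, higher value, which could favour control. Controls who take up exercise would dilute the difference. The net direction is uncertain.
- *That the primary result is compromised.* Spirometry by assessors who are meant to be blinded is much less exposed, and nothing in the documents gives a size for that route.

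This is a cheap improvement and does not challenge the design.

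**What to change.** In section 2.3, and in any recruitment material that repeats it, replace the safe-and-effective statement with a neutral one given in the same words to every candidate: it is not yet known whether adding Baduanjin to basic treatment helps people with mild COPD. State in the protocol that the self-reported outcomes remain open to expectation bias because participants are unblinded, so that differences on them are read with that in mind. Report withdrawals and their reasons by arm, so that any imbalance in retention can be seen.

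The cost is a wording amendment. Section 2.2 requires renewed ethics approval for any amendment, and recruitment may be slightly slower. The interventions, outcomes, sample size and analysis do not change. Patients already recruited under the present message, if any, would keep the expectation it gave them.
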